### Intervention

In the mentioned pilot study the overshadowing treatment known from the paradigm of classical conditioning was tested on pediatric cancer patients. To increase efficiency and applicability, an overshadowing technique known from Broberg and Bernstein will be used [34]. Implementing overshadowing in the hospital’s daily routine requires easy handling and regard to the high hygienic standards on the oncology ward, although in the proposed study the experimental group will receive salient candy and the control group flavorless placebo tablets instead of drinks. During three chemotherapy cycles the experimental group will get their treatment (candy) prior to each infusion. To avoid influences of possible aversive taste reactions, the flavor of candy will be changed from infusion to infusion.

Determining an evaluation period of three cycles can be seen as a compromise. On the one hand, more cycles may increase the intervention effect compared with the placebo condition. On the other hand, more cycles also increase the danger of withdrawals, missing data and comparability of participants and their treatment as the total number of treatment cycles differs widely between low-risk Hodgkin lymphoma and Ewing sarcoma, for example. Three cycles are thus a trade-off between a large effect size and threatened data quality. The pilot study [37] and the basic research [39] showed that even less than three cycles – where each comprises several unconditioned stimulus–conditioned stimulus pairings – is sufficient. However, to determine the applicability of the intervention in daily clinical routine (the third subgoal), the overshadowing treatment in the experimental group will be continued until the end of treatment without any further outcome assessment whenever possible.

### Measures

#### Measuring nausea and vomiting

Symptoms of nausea and emesis will be measured using discomfort logs administered by patients. These logs have been successfully used in our pilot study [37]. They assess nausea and vomiting on 6-point Likert scales focusing on intervals of 2 hours, thus leading to 12 ratings every day. Children from 4 to 7 years of age will be interviewed by a blinded interviewer about their symptoms, and also parents will be asked about their observations. Children from the age of 8 years will use a self-assessment version.

As a second measure, the combined nausea and vomiting scale Baxter Retching Faces (BARF) by Baxter and colleagues will be used [40]. BARF uses a 6-point visual analogue scale with six comic faces expressing mimics ranging from neutral mood to vomiting. The authors developed the BARF scale for children aged from 4 to 17 years. The validation study confirms reliability and validity among patients from 7 to 18 years old. In our study, the BARF scale will be administered by all patients.

There will be two measurement points: the anticipatory measurement phase prior to the third chemotherapy cycle, and also the post-treatment phase after the third chemotherapy cycle (see Figure 1 and Table 4).

**Table 4 T4:** Planned measurements for study aims and subgoals

**Measurement**	**Pre-chemotherapy cycle 3 (anticipatory), t1**	**Post-chemotherapy cycle 3, t2**
Nausea and vomiting (discomfort log, BARF)	X	X
Anxiety (KAT-II, STAI)	X	
Quality of life (Kiddy-KINDL, Kid-KINDL, Kiddo-KINDL)		X
Adherence (caregivers and physicians questionnaires)		X

*BARF*, Baxter Retching Faces; *KAT-II*, Kinder-Angst-Test (Children Anxiety Test); *KINDL*, German Children's Quality of Life Questionnaire (Kiddy/Kid/Kiddo version for each age group); *STAI*, State and Trait Anxiety Inventory.

#### Measuring anxiety

The Kinder-Angst-Test-II/Children Anxiety Test-II [41] is a revision of the questionnaire for German-speaking children and adolescents referring to the trait concept developed in 1969. The trait scale for measuring the anxiety disposition was kept and extended to aspects of state anxiety and was normalized. The revised Kinder-Angst-Test-II consists of three questionnaires, acquiring two different aspects of anxiety. One questionnaire (Form A) appraises trait anxiety, whereas the two others (Form P, Form R) appraise the state anxiety, particularly the anticipated respectively reminded anxiety. The age range for application reaches from 9 to 16 years.

Form A consists of 20 items. The questionnaires Form P and Form R consist of 12 items each, with differences to the referred time period. To operationalize state anxiety, questionnaire Form P will be used prior to the third chemotherapy cycle (see Table 4).

The State and Trait Anxiety Inventory [42] is a self-report inventory with 20 items each for trait and state anxiety (two questionnaires). Items are rated on a four-level scale, ranging from not at all to very, to measure the intensity of anxiety. Adolescents older than 15 years will be only asked to complete the state anxiety questionnaire. The state scale will be assessed prior to the third chemotherapy cycle (see Table 4).

#### Measuring quality of life

The German Children's Quality of Life Questionnaire (KINDL) – Revised is a quality-of-life questionnaire for children with 24 items and allows assessments of six domains: physical well-being, psychological well-being, self-esteem, family, friends, and daily function [43]. Reliability scores (Cronbach’s α = 0.85) and validity of the instrument are confirmed [44]. There are three different self-assessment versions and two parents’ versions: Kiddy-KINDL interview for children aged from 4 to 7 years of age, Kid-KINDL for children aged from 8 to 12, Kiddo-KINDL for adolescents aged from 13 to 16, Kiddy-KINDL parent’s version for children aged from 4 to 7, and KINDL parent’s version for children and adolescents aged from 8 to 16 years of age.

To assess quality of life, pediatric patients will complete the KINDL-R versions after the third chemotherapy cycle (see Table 4).

#### Measuring adherence

Adherent behavior will be obtained through ratings from caregivers and physicians. As in the primary study, the caregivers and physicians administer a questionnaire with eight items to assess the adherent behavior of the children and adolescents. Answers – for example, the intake of medicine – can be rated on a four-level scale from poor to very good (poor, a little, good, very good). The rating of patients’ adherent behavior will proceed after the third chemotherapy cycle (see Table 4).

### Statistical analysis

The effect of the overshadowing treatment on both anticipatory (t1) and post-treatment nausea and vomiting, anxiety, quality of life and adherence (t2) will be analyzed using analysis of covariance comparing mean scores of intervention and control group while controlling for dosage of antiemetics. To account for different appropriate absolute dosages (mg/kg or mg/m^2^) among different patients and drugs, the variable dosage will be operationalized as the percentage of the recommended maximum dosage for each patient and drug. The assumed dependence between the prevalence of post-treatment (t2) and ANV (t1) will be determined by Pearson correlation coefficient.

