**Methods/Design:**

Fifty-two pediatric cancer patients will be evenly assigned to two groups: an experimental group and a control group. The participants, hospital staff and data analysts will be kept blinded towards group allocation. The experimental group will receive during three chemotherapy cycles a salient piece of candy prior to every infusion, whereas the control group will receive flavorless placebo tablets.

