**Discussion:**

If an effectiveness of the overshadowing technique is proven, implementation of this treatment into the hospitals’ daily routine will follow. The use of this efficient and economic procedure should aid a reduced need for antiemetics.

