### Post-treatment nausea and emesis

Chemotherapy-induced nausea and/or emesis are commonly classified as acute, delayed, anticipatory, breakthrough or refractory [5]. Acute onset usually occurs within a few minutes to 1 or 2 hours after infusion and resolves within the first 24 hours. Delayed onset emesis begins or persists more than 24 hours after chemotherapy treatment. Anticipatory nausea and emesis occurs before patients receive their chemotherapy administration. Breakthrough emesis occurs despite prophylactic treatment and requires rescue antiemetics. Refractory emesis arises during subsequent treatment cycles when antiemetic prophylaxis and rescues have failed in earlier cycles.

Chemotherapy-induced nausea and vomiting differs from that usually experienced – it lasts longer, its degree of severity varies from treatment to treatment and there is a greater variability in patient reaction. For example, anxiety, personality and environment seem to play a key role. Factors that increase the risk of nausea and emesis beside pharmacological (dosage, agent, duration) are age, gender and expectation of these adverse effects [6].

Initiation and coordination of the emetic process is the responsibility of the vomiting center, a structure located in the lateral reticular formation of the medulla. Afferent input from several sources, including the higher brain stem and cortical structures, are capable of initiating the emetic process [7].

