### Sample size calculation

The calculation of the required sample size is oriented towards the demands of the first study question, which addresses the effect of overshadowing on ANV (primary endpoints). The effect sizes that were achieved in our pilot study for reduction of ANV are to be judged as very large in view of statistical conventions (effect sizes in *t* tests were *d* = 2.5 (nausea) and *d* = 1.4 (vomiting)). For the present study, a more conservative effect size of *f* = 0.4 in analysis of covariance (see below) is assumed. Aiming at a statistical power of 0.80, a total sample size of *n* = 52 is needed (two-sided α = 0.05).

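### The only ANCOVA covariate, antiemetic dosage, is not tied to a value fixed before randomisation and may be lowered by the intervention, so the adjusted effect may be biased

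*Protocol article*

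**What the plan says.** The Statistical analysis section applies one model to anticipatory symptoms (the primary endpoints), post-treatment symptoms, anxiety, quality of life and adherence. It is an analysis of covariance "comparing mean scores of intervention and control group while controlling for dosage of antiemetics". The covariate is then defined: "the variable dosage will be operationalized as the percentage of the recommended maximum dosage for each patient and drug". The section gives no time window and does not separate prophylactic from rescue doses.

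Other sections place this dosage in time and in relation to symptoms:

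- **Participants:** patients are newly diagnosed and should not have had treatment-related nausea or vomiting before.
- **Intervention:** candy or placebo is given before infusions over three cycles.
- **Measures and Table 4:** outcomes are taken before cycle 3 (t1) and after it (t2).
- **Abstract and Aims of the study:** less post-treatment nausea and vomiting is an intended effect.
- **Post-treatment nausea and emesis (Background):** "Breakthrough emesis occurs despite prophylactic treatment and requires rescue antiemetics".

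The Study design section gives the likely reason for the adjustment. Diagnosis determines the cytostatics, and these influence which antiemetics are used. Randomisation is therefore blocked within diagnosis.

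**The concern.** A covariate in a randomised comparison is safe when allocation cannot have influenced it. Antiemetic dosage, as defined here, does not clearly meet that condition. By t1 a child has been through two treated cycles. If the candy has reduced symptoms in those cycles, fewer rescue doses may have been needed, and the recorded percentage of the maximum dosage may be lower in the experimental arm for that reason.

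Adjusting for such a variable compares arms at equal dosage. The total effect of being assigned to overshadowing is a different quantity. If children with more symptoms receive more antiemetic, the adjustment takes away part of a real benefit. The trial is planned for 80% power with no margin, so a modest loss matters. The same covariate enters every secondary analysis, where the size of any bias may differ by outcome.

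**Working it through.** **Inputs from the article.** Sample size calculation: "a more conservative effect size of *f* = 0.4 in analysis of covariance"; "Aiming at a statistical power of 0.80"; two-sided alpha 0.05; total 52. Abstract: "Fifty-two pediatric cancer patients will be evenly assigned to two groups", so 26 per arm.

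**Step 1: reproduce the planned sample size.** With two equal groups, d = 2f = 2 × 0.4 = 0.80. The F test has 1 and N − 2 − c degrees of freedom, where c is the number of covariate terms, and noncentrality f² × N = 0.16 × 52 = 8.32. The smallest N with power of at least 0.80 is 52 for c = 0, 1 or 2, and power at 52 is 0.807 in each case. The stated 52 is correct.

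**Step 2: the bias formula.** Scale outcome and dosage to a within-arm SD of 1. Let s be the reduction in mean dosage caused by the intervention and ρ the within-arm correlation of dosage with symptoms. Then

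adjusted benefit = total benefit − ρ × s.

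The bias is zero if s = 0 or if ρ = 0. It is towards no effect if ρ is positive and away from it if ρ is negative.

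**Step 3: put numbers in.** The article gives neither s nor ρ, so both are assumed. The planned 0.80 is taken as the total benefit in within-arm SD units. Power is from simulation with 26 per arm and 5,000 runs per row. Unadjusted power was about 0.80 to 0.81 in these rows.

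| s (SD) | ρ | Adjusted benefit | Power, adjusted |
|---|---|---|---|
| 0 | 0.3 | 0.80 | 0.83 |
| 0 | 0.5 | 0.80 | 0.90 |
| 0.3 | 0.3 | 0.80 − 0.09 = 0.71 | 0.74 |
| 0.5 | 0.3 | 0.80 − 0.15 = 0.65 | 0.63 |
| 0.5 | 0.5 | 0.80 − 0.25 = 0.55 | 0.57 |
| 0.8 | 0.5 | 0.80 − 0.40 = 0.40 | 0.33 |
| 0.5 | −0.3 | 0.80 + 0.15 = 0.95 | 0.92 |

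The first two rows show what adjustment would gain if allocation did not move dosage. The last shows that the effect can also be exaggerated.

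**Step 4: no total effect.** If the intervention lowers dosage by 0.5 SD but does not change the outcome, two-sided rejection is 0.085 at ρ = 0.3 and 0.167 at ρ = 0.5, against a nominal 0.05. With positive ρ the spurious difference points towards harm, so it would not produce a false claim of benefit.

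**Step 5: cost of replacing the covariate.** Dropping dosage, or exchanging it for one or two pre-randomisation terms, leaves power at 0.807 for f = 0.4. The number of diagnosis strata is not stated. With c = 10 the same formula gives 0.804 at N = 52.

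**The case against.** The article's own account is that antiemetic use follows the cytostatics, and the Limitations section treats antiemetics as a matter of balance alongside diagnosis. Prophylaxis set by the regimen would not differ by arm, and if it made up the whole covariate there would be no bias and some gain in precision. The time window could also be fixed in a fuller protocol or analysis plan. This stands in part. The timing is inferred, and a definition limited to prophylaxis planned before allocation would remove the problem. But the covariate is named, defined and applied to the primary endpoints without that limit. The Antiemetics section itself says that limited standardisation may lead to widely varying strategies. Concern about regimen differences justifies adjusting for diagnosis or planned regimen, and does not require dosage given later.

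The numbers can also be challenged. The article reports no effect of overshadowing on dosage, and small shifts do little harm. If antiemetics themselves reduce nausea, the within-arm association could be weak or negative. That is correct, and it is why the size is shown as a range.

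Three stronger readings are tempting but not supported:

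- **That every adjusted effect is biased.** Bias needs both conditions in Step 2, outcome by outcome.
- **That the trial hypothesises a lower dose.** The sentence "The use of this efficient and economic procedure should aid a reduced need for antiemetics" follows a statement about implementation once effectiveness is shown. It concerns later routine use, and the Aims list no antiemetic endpoint.
- **That dosage is nearly part of the adherence outcome.** Intake of medicine is one example from an eight-item rating and is not specific to antiemetics.

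**Conclusion.** The point holds as a risk built into the stated analysis. The sole covariate is open to influence by allocation through a route that the article itself describes: fewer symptoms, then fewer rescue doses. The adjusted comparison therefore need not estimate the total effect of overshadowing. The most plausible direction is towards no effect, provided that more symptoms lead to higher dosage. Moderate assumed values take d from 0.80 to between 0.71 and 0.55, and power from about 0.80 to between 0.74 and 0.57. These figures rest on an assumed dose shift and correlation and on a linear model, and they are not predictions for this trial. The sample size calculation is sound.

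**What to change.** In the Statistical analysis section, let the primary analysis of covariance adjust only for factors fixed before randomisation. The first choice is the diagnosis stratum already used for randomisation. If wanted, add the MASCC emetic-risk class of the planned regimen or the prophylaxis planned before allocation. Report administered antiemetic dosage by arm, using the percentage definition already given. Keep the dose-adjusted model as a sensitivity analysis, labelled as adjusting for a variable that treatment may affect, and state the time window and whether rescue doses are included.

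The cost is a change of wording, a few degrees of freedom for the strata, and the loss of whatever outcome variance dosage would have explained. N = 52 stays as it is. Very sparse diagnoses may have to be grouped, by a rule set before the data are seen.

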A limited search focusing on cancer leads to four articles about the scapegoat effect on food aversion from cancer patients [32-35], while two articles consider the overshadowing effect on conditioned nausea [10,36]. Of these, just one describes an investigation among pediatric cancer patients [34]. Screening of the reference lists of these articles did not add any previously unconsidered publications.

Broberg and Bernstein used a scapegoat technique to prevent food aversion in children undergoing chemotherapy [34]. Patients received candy (coconut and root beer Lifesavers) between the consumption of a meal and administration of chemotherapy. Children who received the candy, which served as a scapegoat, were twice as likely to eat some portion of a future test meal.

Stockhorst and colleagues investigated 16 adult cancer patients with an overshadowing protocol using salient drinks to prevent anticipatory nausea and emesis [10]. The experimental group (*n* = 8) received salient drinks before administration of drug infusions through two cycles of chemotherapy, while the control group received water. In the third cycle of chemotherapy all patients received water. Patients receiving an overshadowing treatment did not develop anticipatory nausea, whereas two patients of the control group did. Furthermore, overshadowing tended to modify the occurrence of post-treatment nausea: it occurred later and was of shorter duration. The results are not statistically significant because of a quite small sample size; they only suggest tendencies.

In a pilot study at our medical center, Görges adapted the study design of Stockhorst and colleagues [10] for the pediatric setting (*n* = 30), where overshadowing proved to be effective [37]. No patient of the overshadowing group (*n* = 15) developed anticipatory nausea, compared with 13 patients of the control group. Furthermore, overshadowing reduced the occurrence of concomitant symptoms such as anxiety, nonadherent behavior and affected well-being. Overshadowing also seemed to decrease the intensity of post-treatment nausea. However, the partially insufficient feasibility of the used intervention technique led to problems of recruitment. This problem may have biased the results towards an overestimation of the intervention effect. Such threats of validity have to be avoided in the present study. Additionally, reducing the complexity of the intervention increases the chances of implementation into daily clinical routine.

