### Aims of the study

The aims of the present study were to verify the effect of an optimized overshadowing technique on ANV (primary endpoints), and to further investigate the intervention effect on post-treatment nausea and vomiting (secondary endpoints). The subgoals were to investigate the overshadowing effect on patients’ quality of life, state anxiety and adherence; to survey the relation between prevalence of post-treatment and ANV; and to determine the applicability of the overshadowing treatment in the hospital’s daily routine.

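### The planned Pearson correlation between ANV (t1) and post-treatment symptoms (t2) has no stated adjustment for arm, so it may partly reflect the treatment effect

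*Protocol article*

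**What the plan says.** The Aims of the study section lists, among the subgoals, "to survey the relation between prevalence of post-treatment and ANV". The Statistical analysis section gives the method in one sentence: "The assumed dependence between the prevalence of post-treatment (t2) and ANV (t1) will be determined by Pearson correlation coefficient". The same paragraph describes an analysis of covariance that compares the arms and adjusts for antiemetic dosage. Neither the arm nor the dosage is carried over to the correlation. The article also does not say in so many words that the arms are pooled.

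On timing, the section on measuring nausea and vomiting says "There will be two measurement points". Table 4 places t1 before the third cycle and t2 after it.

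The Aims section makes the effect of overshadowing on ANV the primary question and its effect on post-treatment symptoms the secondary one. The trial therefore hopes to move both variables that enter the correlation. For post-treatment symptoms the only pilot evidence is qualitative: "Overshadowing also seemed to decrease the intensity of post-treatment nausea".

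**The concern.** When a randomised treatment shifts two variables in the same direction, the arm means line up along a rising diagonal. A correlation over both arms picks up that alignment even if, among children in the same arm, those with more ANV have no more post-treatment symptoms than the others. The coefficient then partly re-expresses the treatment effect, whereas the subgoal asks how the two symptoms are related. The relevant quantity is the association between children within an arm. Each child contributes one t1 and one t2 summary, so no within-child relation can be estimated.

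The stake is limited to how this subgoal is interpreted. A reader could take a positive coefficient as evidence that the two symptoms go together when part of it comes from the intervention. If treatment moves only ANV, the error runs the other way and a real association is understated.

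**Working it through.** **Inputs.** Total 52, evenly allocated, so 26 per arm (Abstract; Sample size calculation). Planning effect: "a more conservative effect size of *f* = 0.4 in analysis of covariance (see below) is assumed", which for two equal arms is d = 2f = 0.8. Pilot effects on ANV: d = 2.5 for nausea and 1.4 for vomiting (Sample size calculation). The article gives no effect size for t2, so every t2 value below is an assumption, shown as a range.

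**The plan's own figure.** With f = 0.4, two-sided alpha 0.05 and N = 52, the noncentrality is 52 × 0.4² = 8.32. The noncentral F test has power 0.807 with no covariate or with one, and 52 is the smallest N that reaches 0.80. The stated sample size reproduces.

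**Pooled correlation.** For a 1:1 mixture of two arms with equal within-arm SDs, within-arm correlation w, and effects d1 (t1) and d2 (t2) in within-arm SDs:

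r = (w + d1·d2/4) / √[(1 + d1²/4)(1 + d2²/4)]

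With w = 0:
- 0.8 and 0.8: 0.16 / 1.16 = 0.14
- 0.8 and 0.4: 0.08 / √(1.16 × 1.04) = 0.07
- 1.4 and 0.8: 0.28 / √(1.49 × 1.16) = 0.21
- 2.5 and 0.8: 0.50 / √(2.5625 × 1.16) = 0.29
- 0.8 and 0, or 2.5 and 0: 0

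**Chance of p<0.05 when w = 0.** From 20,000 simulated trials per scenario, 26 per arm, normal scores, equal variances:

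| d at t1 / d at t2 | pooled r | pooled test rejects | arm-adjusted test rejects |
|---|---|---|---|
| 0.8 / 0 | 0.00 | 5% | 5% |
| 0.8 / 0.4 | 0.07 | 8% | 5% |
| 0.8 / 0.8 | 0.14 | 16% | 5% |
| 1.4 / 0.8 | 0.21 | 34% | 5% |
| 2.5 / 0.8 | 0.29 | 58% | 5% |

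The arm-adjusted coefficient averages 0.00 in every row. For 0.8 / 0.8 a Fisher z calculation agrees: atanh(0.138) × √49 = 0.97, which gives 16%.

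**Dilution.** If w = 0.30 and treatment affects only t1, the pooled r is 0.30/√1.16 = 0.28 at d1 = 0.8 and 0.30/√2.5625 = 0.19 at d1 = 2.5.

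**The case against.** The strongest reply is that pooling is inferred from silence. One sentence in a journal article names a coefficient, and a full protocol or analysis plan that is not shown may adjust for arm. It is right that pooling is not stated. Still, the sentence fixes a method for a named subgoal, and that method as written has no arm term, although the sentence on the ANCOVA does compare the arms.

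It can also be said that this is a descriptive subgoal with no test or threshold attached, so a chance of significance is not a planned decision. That stands. The rejection rates only show how often the artefact would look convincing.

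Several stronger readings are tempting but not supported:
- *A successful trial would by itself confirm the dependence.* This needs a sizeable effect at t2, and none is given. Setting d = 1.4 at both times yields r = 0.33 and about a two-in-three chance of significance (67% by Fisher z, 71% by simulation), but 1.4 is the pilot effect on anticipatory vomiting, moved to a different outcome.
- *The time order is reversed.* Under the conditioning account, earlier post-treatment symptoms would precede ANV, whereas t2 follows t1. But the article speaks only of dependence, and a correlation is symmetric. No causal claim is made, so only clear labelling is needed.
- *The scores are mostly zero.* No score distribution is given, and 13 of the 15 pilot controls developed anticipatory nausea.

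**Conclusion.** The point holds as a minor one. Followed as written, the correlation mixes the treatment shift with the association among children in a trial that aims to shift both variables. At the planning effect applied to both times the distortion is small: r about 0.14 where the within-arm value is 0, with the false-positive rate rising from 5% to about 16%. It grows only if effects approach the pilot's, and it disappears if treatment does not affect t2, leaving dilution instead.

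This rests on three assumptions: that the arms are pooled, that the t2 effects lie in the range shown, and that within-arm variances are equal, with roughly normal scores for the rejection rates. Six-point ratings could change the sizes but not the direction. The primary ANCOVA and n = 52 are untouched.

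**What to change.** Amend the one sentence in the Statistical analysis section:
- Make the arm-adjusted partial correlation the main figure for this subgoal, preferably rank-based because the ratings are 6-point ordinal.
- Show the within-arm coefficients descriptively, where they can be estimated.
- Describe the result as the association of ANV before cycle 3 with symptoms after cycle 3.

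No new data are needed, and the main figure costs one degree of freedom (49 instead of 50). The within-arm values have a cost in interpretation. In the pilot none of the 15 overshadowing patients developed anticipatory nausea. If that recurs, the experimental-arm coefficient for nausea is undefined or uninformative. With 26 children, the power to detect a true r of 0.30 is about 32%, against about 58% with 52 (Fisher z). The within-arm values should therefore not carry the conclusion.
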